**Table 2 T2:**
[figure not shown]
Template of adverse events of herbal medicine.

### Data management and quality control

2.7

The data collection uses the eCRF system (myTrial electronic data capture) verified by IT-KoM. The KM doctors in charge of each clinic will check the clinical measurement results of the participant assessed at each visit, and then, will input and save them into the eCRF system. To access a data entry form, each KM doctor on a remote computer with an internet connection enters the address of the web server (http://ecrf.nikom.or.kr). Then, a login screen is displayed and the each user enters a user identification and password, provided by personnel responsible for the web site. Each case entered into the registry will be periodically reviewed, and data queries will be generated to provide feedback to the KM clinics by a clinical research associate, based on the data monitoring manual. Data for this study will be stored safely in a dedicated collection server and this server will grant limited data access rights.

### Sample size calculation

2.8

We plan to recruit at least 1000 patients during this study period. Empirically considering the trends of the patients visiting each primary KM clinics, we estimated that approximately 1000 participants will be enrolled (65 patients or more per year per clinic) for a year. The study started in October 2021, is currently ongoing, and will finish in October 2022.

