**Methods and analysis::**

This is a prospective, observational, multi-center registry, including patients visiting the KM clinics in South Korea for weight loss. This study will collaborate with 15 KM clinics and recruit patients into the registry between October 2021 and October 2022. The study population will include patients visiting the KM clinics for weight loss. A total of 1000 eligible patients visiting the KM clinics for weight loss who decide to undergo HM treatment will be enrolled in the registry. After enrollment, we will collect the individual characteristics of each patient, such as body mass index, body composition test, liver and kidney function tests, and information on prescribed HM. We will also record the adverse events at each visit.

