### Study design/setting

2.1

This is a prospective observational multi-center study enrolling patients undergoing KM weight loss treatment in Korea. We will recruit patients from the following 15 KM clinics: Bareun-mom S KM clinic (Hwaseong, Gyeonggi-do), Saeng-saesang KM clinic (Daejeon), Sangju Baraeun KM clinic (Sangju, Gyeongsang-do), Hwapyeong KM clinic (Incheon), Imom KM clinic (Changwon, Gyeongsang-do), Goeun KM clinic (Gunpo, Gyeonggi-do), Lee Seung Jin KM clinic (Namyangju, Gyeonggi-do), Onki KM clinic (Namyangju, Gyeonggi-do), Chunjin KM clinic (Boryeong, Chungcheon-do), Sogood KM clinic (Seongnam, Gyeonggi-do), Gyeongsan S KM clinic (Gyeongsan, Gyeongsang-do), Myoungjak KM clinic (Gunsan, Jeolla-do), Momandjang KM clinic (Gunpo, Gyeonggi-do), Kyurim KM clinic (Cheongju, Chungcheon-do), and Madimadi KM clinic (Yongin, Gyeonggi-do) between October 2021 and October 2022 (Fig. 1). Patients who provide informed consent to participate will receive KM weight loss treatment according to their individual characteristics without any intended intervention. At baseline (recruitment), comprehensive data will be collected on the following variables: demographics, anthropometric information, medical history, laboratory tests, treatment, and AEs. An electronic care report form (eCRF) was developed using the myTrial system^[19]^ of the National Agency for Development of Innovative Technologies in Korean Medicine (IT-KgoM), which supports public eCRFs. Table 1 shows the data collection and follow-up schedules.

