**Figure 1 F1:**
[figure not shown]
Study flow chart. BMI = body mass index, BP = blood pressure, KM = Korean medicine.

**Table 1 T1:** Study schedule of the registry study.

	Enrollment baseline	Subsequent visits	End of treatment
Informed consent	V		
Eligibility screening	V		
Demographic characteristics	V		
Body mass index	V		V
Body composition test	V		V
Liver function tests	V		V
Kidney function tests	V		V
Herbal medicine	V	V	V
Blood pressure, body temperature, pulse rate	V		V
Adverse event		V	V

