### Recruitment

2.4

The participants will be recruited from KM obesity clinics of 15 KM primary medical institutions across Korea. The researcher will fully explain the aim of this study and details of the procedures, including research usage, confidentiality, and providing data provision to third parties for analysis and will obtain informed consent from the potential participants who met the inclusion criteria before the collection of information.

Participants will be free to withdraw at any time during the study, and this will not affect their clinical treatment. We encourage voluntary participation in this study by posting recruitment posters on the walls of the entrance and elevators of the each clinic.

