### Outcomes measures

2.6

Researchers determined that the following data will be collected for observing the characteristics of KM weight loss treatment. Detailed research schedule and variables are presented in Table 2.

(1)*Demographics*: Age, sex, and medical history will be collected as basic demographic information.(2)*Anthropometric data*: If a participant visits physically for consultation, vital signs, including blood pressure, body temperature, and pulse rate will be collected as variables related to general health conditions. Weight, height, and body mass index (BMI) will be measured as variables for weight change. Body fat mass, body muscle, visceral fat level, etc will be measured as variables for changes in body composition.(3)*Liver and kidney function tests*: To evaluate the physical changes induced by long-term administration of HM or weight loss, liver function (aspartate aminotransferase, alanine aminotransferease) and renal function tests (blood urea nitrogen, creatinine) will be conducted at the visit.(4)*Other laboratory test*: Total cholesterol, high-density lipoprotein, low-density lipoprotein, triglycerides, etc will be evaluated at the visit to evaluate the physical changes induced by long-term administration of HM for weight loss.(5)*HM treatment*: For the observation and collection of real clinical data, there will be no restriction on the type or frequency of HM treatment, and doctors in the primary KM clinics will perform the HM treatment according to the characteristics of the individuals. For a given period, prescription medication will be recorded with the name of the medicine, medicine composition, and treatment duration.(6)*AEs*: At each treatment visit, participants will be investigated by the KM doctors using the AEs template developed by the expert Delphi group to evaluate the occurrence of any AE. In case of occurrence of any AE, we will immediately provide appropriate treatment to the participant according to the guidelines of the clinic, and then observe the participant's progress during the follow-up visit. The name, severity, and duration of the AEs that occur during the study period will be recorded. In addition, any causality assessments between the AE and the KM treatment will be evaluated by the investigator during visits. All investigators and KM doctors will be educated in research ethics (Table 2).

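### Recruitment and the study both end in October 2022, leaving no stated follow-up for patients enrolled late and still on treatment

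*Protocol article*

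**What the plan says.** The abstract of the protocol article states that the registry will "recruit patients into the registry between October 2021 and October 2022", and section 2.1 (Study design/setting) gives the same window. Section 2.8 (Sample size calculation) states: "We plan to recruit at least 1000 patients during this study period". It expects that "approximately 1000 participants will be enrolled (65 patients or more per year per clinic) for a year", and it ends with "The study started in October 2021, is currently ongoing, and will finish in October 2022". Section 2.4 (Recruitment) names "15 KM primary medical institutions across Korea" as the source of patients.

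Table 1 has three columns: baseline, subsequent visits, and "End of treatment". BMI, body composition, liver function, kidney function and vital signs are marked at the first and last only. Adverse events are marked at subsequent visits and at the last.

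Section 2.6 (Outcomes measures) gives the reason for the liver and kidney tests: "To evaluate the physical changes induced by long-term administration of HM or weight loss". It places no limit on the type or frequency of herbal treatment and sets no course length. Section 2.9 (Statistical analysis) plans paired pre-post comparisons and fills missing values by LOCF.

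**The concern.** Accrual and the whole study occupy the same calendar window. Before-and-after results need a second measurement, and Table 1 places that measurement at the end of treatment. A patient who enrols late and is still on treatment when the study closes has a baseline and nothing to compare it with.

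The loss is not random with respect to exposure. The longer the course, the more likely it is to be cut off, so the completed courses over-represent short ones. The liver and kidney panels were included to look at prolonged use, so the patients who matter most for them are the ones most often lost.

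The missing-data rule can add a second problem. If an end-of-treatment value that never fell due is treated as missing and replaced by the last value, the baseline is compared with itself. An unobserved patient is then recorded as unchanged, both for weight and for organ function.

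**Working it through.** **Inputs from the protocol article.** Recruitment window October 2021 to October 2022 (abstract, section 2.1). Study start and finish in the same two months (2.8). 15 clinics (2.4). 65 or more patients per clinic per year, target about 1000 (2.8). Post-baseline measurements of BMI, body composition, laboratory tests and vital signs at end of treatment only (Table 1).

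**Assumed, because the document does not give it.** Course length T, shown for 0.5 to 6 months, and uniform accrual over W months.

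**Step 1: the plan's own figure.** 15 × 65 × 1 year = 975, which is 2.5% below 1000. Exactly 1000 needs 1000 / 15 = 66.7 per clinic, consistent with 65 or more. The target therefore reproduces as a feasibility estimate. It also shows that accrual is expected to fill the year, so early completion of recruitment cannot be counted on to create follow-up time.

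**Step 2: share cut off before the end of treatment.** Under uniform accrual, a patient with course length T is cut off if enrolled in the last T months, so the share is T / W.

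| T (months) | W = 12: share | of 1000 | W = 13: of 1000 |
|---|---|---|---|
| 0.5 | 4.2% | 42 | 38 |
| 1 | 8.3% | 83 | 77 |
| 2 | 16.7% | 167 | 154 |
| 3 | 25.0% | 250 | 231 |
| 6 | 50.0% | 500 | 462 |

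W = 13 reads the window as 1 October 2021 to 31 October 2022. Mean available follow-up is W / 2, that is 6 to 6.5 months, and it falls to zero for the last enrollees.

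**Step 3: selection by course length.** The share of courses seen to their end is 1 − T/12: 11/12 = 92% of 1-month courses, but 6/12 = 50% of 6-month courses.

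**Step 4: effect of LOCF, if applied to these patients.** With measurements at baseline and end of treatment only, the value carried forward is baseline and the change is 0. If the true mean change is the same, D, in everyone, the analysed mean is D × (1 − T/12): 0.92 D for 1 month, 0.75 D for 3 months and 0.50 D for 6 months. If a clinic happens to record an interim value, that value is carried instead and the dilution is smaller, but Table 1 schedules none.

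**Step 5: would closing enrolment early solve it?** At 65 per clinic per year, stopping T months before a fixed October 2022 end gives 975 × (12 − T)/12 patients: 894 for 1 month, 731 for 3 months, 488 for 6 months. All fall short of the stated 1000.

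**The case against.** The strongest reply is that the closing sentence of section 2.8 sits in a paragraph about enrolment and may only restate the recruitment window. The article condenses a fuller protocol (version 1.2), the flow chart is not visible here, and a last-follow-up date is a detail an article may leave out. That reading is possible. But the sentence speaks of the study, not of recruitment, and nothing in the article gives a later cut-off. The point rests on dates that are stated and that do not fit the visit schedule, so under either reading the sentence needs correcting.

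Several stronger conclusions that a reader might infer are not supported:

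- That no late enrollee can reach the end-of-treatment visit. A short course may well finish before close, and course length is unrestricted.
- That 83 to 500 patients lack safety data. Adverse events are collected at every subsequent visit, so a patient cut off mid-course contributes events up to that time. Only those with no return visit at all before close have none.
- That the 1000 is miscalculated or falls short of a promise. It is an enrolment target based on feasibility. It is not a number of completers, and no power claim hangs on it.
- That the registry fails a long-term aim. The two aims listed in the Introduction are clinical characteristics with current status, and safety. Prolonged use appears as the rationale for the laboratory tests, and early enrollees can have up to 12 months of observation.
- That LOCF will certainly be applied to visits not yet due. Section 2.9 does not say whether such visits count as missing. It also does not exclude them.

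**Conclusion.** The point stands as a conflict between the stated dates and the stated schedule. Followed as written, the plan has no follow-up period after the last enrolment, and late enrollees still on treatment at close lack the post-treatment measurements. The loss falls more heavily on longer courses.

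The size cannot be derived from the document. It is T/12 under uniform accrual and an assumed course length, so it could be a few percent or as much as half. The dilution of the pre-post change is conditional on two further assumptions: that LOCF is used for these patients, and that the true change is equal in all of them.

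For a descriptive registry without a confirmatory hypothesis, this should be fixed, but it does not invalidate the study. It is best settled while the registry is still running, because follow-up not collected before close may not be recoverable.

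**What to change.** Reconcile the dates by separating two milestones. Keep October 2022 as the date of last enrolment, and state a data cut-off a fixed number of months, M, after it. A fixed interval is preferable to waiting for the last patient to finish, since treatment length has no upper limit. The sponsor can choose M from the treatment durations already being recorded in the eCRF.

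With this change every enrollee has at least M months available. Courses up to M months are no longer cut off, and for longer ones (up to M + 12 months) the share falls from T/12 to (T − M)/12. For example, M = 3 takes a 3-month course from 25% to 0 and a 6-month course from 50% to (6 − 3)/12 = 25%.

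In section 2.9, add that patients still on treatment at the cut-off are reported as administratively censored, with their number and time on treatment, and that their end-of-treatment values are not filled by LOCF in the pre-post analysis. This removes the artificial zero changes. It does not by itself remove the under-representation of long courses, which is why the later cut-off is also needed.

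The cost is a short amendment, an update of the registration, and a database close some months later at the existing clinics with the existing eCRF. Closing enrolment early to keep October 2022 as the study end is not recommended, because it would miss the stated 1000 (about 731 patients if three months are given up).

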### Statistical analysis

2.9

All statistical analyses will be conducted via two-tailed tests, and the significance level will be set at 5%. Categorical variables will be presented as n (%) whereas continuous variables will be expressed as mean ± standard deviation. For comparison of two or more groups, categorical variables will be subjected to the chi-square test and Fisher's exact test, whereas continuous variables will be analyzed using the *t* test and analysis of variance or non-parametric methods, such as Mann–Whitney *U* test and Kruskal–Wallis test, for those not meeting the normality criteria. Pre- and post-treatment comparison conducted with a paired *t* test or Wilcoxon signed rank test will be analyzed using a Kolmogorov–Smirnov test. Analysis of covariance will be performed when it is necessary to control the underlying variables, such as demographic variables. For data with a missing value, the last observation carried forward will be used through case report form (CRF) inspection to replace the missing value. All statistical analyses in this study will be conducted using SAS software, version 9.4 (SAS Institute, Inc., Cary, NC).

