The purpose of this study is to investigate the clinical characteristics and current status of individuals who receive HM for weight loss in KM by constructing multi-institutional prospective registry. Overall, the aims of this registry are to:

(1)investigate the clinical characteristics and current status of treatment for weight loss;(2)evaluate the safety of various HMs for weight loss, based on nationwide registry outcome collecting process.

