This study has great significance. This study is the first registry-based study for collecting real-world data of patients receiving HM for weight loss in primary KM clinics. In South Korea, of the total 15,167 medical institutions affiliated with the KM health industry, KM primary clinics account for approximately 93% with 14,106 institutions. This explains the need of research in primary medical units by observing the real-world data of KM.^[22]^ The result of this registry may show the current status of patients receiving HM treatments for weight loss and provide evidence for reasonable decision-making on KM healthcare policy for obese patients in the future. Second, this study is an intervention-based registry focusing on HM in KM. It has great significance in accurately collecting the prescription composition and dose of HM data for obesity treatment in actual clinical practice on a standardized registry platform. This registry can contribute greatly in providing evidence on the safety of obese patients who have been receiving treatment with HM through large-scale data collection for primary medical institutions. Third, this study will apply the HM AEs template developed through a systematic method by an expert Delphi group. Six types of AEs, including headache, nausea, chest palpitations, dry mouth and thirst, constipation, and insomnia, were statistically determined through the Delphi method (data are not shown) and the terms representing AEs were used according to the Medical Dictionary for Regulatory Activities.^[23]^ It would be helpful to collect systematic AEs of HM for weight loss. Fourth, this registry aims to collect the data of 1000 patients visiting the primary KM clinics. This is the largest KM registry focusing on primary KM clinics. This registry will enroll patients receiving HM for weight loss; thus, a large patient sample can be enrolled to investigate the natural history and clinical characteristics of these patients, including demographics, treatment history and results, and progress.^[24]^ Lastly, this registry data will reflect on the KM clinical practice guidelines for obesity. This study is a part of the project named “Advancement of Korean Medicine Clinical Practice Guideline and Critical pathway for Obesity” that aims to develop and disseminate clinical practice guidelines for obesity in KM.^[25]^ The data will be used to verify hypotheses for KM weight loss treatment, including safety of HM. Moreover, it has been planned to reflect the safety verification results of HM, which are urgently required in the current version of KM clinical practice guidelines,^[26]^ and will contribute greatly to the KM community.

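### The Discussion promises to verify the safety of herbal medicines, but the only inference stated in section 2.9 is two-tailed difference testing, which cannot support that conclusion

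*Protocol article*

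**What the plan says.** The second aim in the Introduction is to "evaluate the safety of various HMs for weight loss, based on nationwide registry outcome collecting process". The Discussion goes further: "The data will be used to verify hypotheses for KM weight loss treatment, including safety of HM". It adds that "it has been planned to reflect the safety verification results of HM, which are urgently required in the current version of KM clinical practice guidelines".

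Section 2.9 (Statistical analysis) sets the inference: "All statistical analyses will be conducted via two-tailed tests, and the significance level will be set at 5" per cent. The summaries are descriptive: "Categorical variables will be presented as n (%) whereas continuous variables will be expressed as mean ± standard deviation". Groups are compared by tests of difference: "For comparison of two or more groups, categorical variables will be subjected to the chi-square test and Fisher's exact test", with t tests, analysis of variance or rank tests for continuous data. Changes over time are handled by "Pre- and post-treatment comparison conducted with a paired *t* test or Wilcoxon signed rank test". Analysis of covariance is added where baseline variables need control. The section names no other form of inference.

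On exposure, section 2.6 says "there will be no restriction on the type or frequency of HM treatment", so the number of patients per formula is left to practice. Section 2.8 bases the target of 1000 on expected clinic volume.

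**The concern.** Each test listed in section 2.9 has no difference as its null hypothesis. Rejecting the null can point to harm. Failing to reject it says only that the data did not separate the groups, which also happens when events are few or a group is small. No result of these tests verifies safety, yet the Discussion promises verification and names a guideline as the destination.

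The descriptive output does not close the gap by itself. A percentage without a bound does not show how much harm remains compatible with the data: 0 of 66 and 0 of 1000 both appear as 0%. Guideline readers who are offered a safety verification need that bound, above all for formulas with few users.

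**Working it through.** **Step 1: the plan's own figure.** Section 2.8 gives 15 clinics and 65 or more patients per clinic per year. 15 × 65 = 975, and 1000 / 15 = 66.7 per clinic, so the target of about 1000 follows. It is a feasibility figure. Section 2.8 states no AE rate, power or precision, so the rates and group sizes below are assumptions.

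**Step 2: what a difference test misses.** Two groups share the 1000 patients: users of one formula against all others. The test is Fisher's exact test, two-sided 5%. The chance of missing a true difference is the sum, over all pairs of event counts with p ≥ 0.05, of the product of the two binomial probabilities. By exact enumeration:

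| Group sizes | 20% v 10% | 10% v 5% | 2% v 0.5% |
|---|---|---|---|
| 100 v 900 | 22% | 52% | 71% |
| 200 v 800 | 5% | 31% | 54% |
| 500 v 500 | 1% | 17% | 52% |

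The first rate is that of the formula in question. The last column is a fourfold difference; the other two are doublings. The miss rate is high for uncommon events, and for moderately common events when the group is small. It is low for common events in larger groups.

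**Step 3: the laboratory tests.** Liver and kidney tests are taken at baseline and at end of treatment, so the paired test applies. The detectable change at 80% power is (1.96 + 0.84) / √n standard deviations (SD). For n = 1000 this is 2.80 / 31.6 = 0.089 SD. For an assumed 300 complete pairs it is 2.80 / 17.3 = 0.16 SD. Power is not a problem here. The risk runs the other way, since a trivial mean shift can reach p < 0.05. That too is better handled by an estimate with its interval.

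**Step 4: what a bound shows.** With zero events, the upper limit of the exact two-sided 95% interval is 1 − 0.025^(1/n):

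- n = 1000: 0.37%
- n = 100: 3.6%
- n = 66: 5.4%

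With an observed rate of 5%, the exact (Clopper-Pearson) 95% interval is 3.7% to 6.5% at n = 1000 and 1.6% to 11.3% at n = 100. Fewer patients give a wider interval and a more cautious statement. A non-significant test behaves in the opposite way: it becomes more likely as the group shrinks.

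**The case against.** The strongest reply is that the plan contains no rule equating non-significance with safety. A reader might infer that p > 0.05 will enter the guideline as proof of safety, or that a formula with few users will be declared safe because it has few users. The article does not say so. The opening of the Discussion cautions that a study of this kind does not guarantee a definitive relationship for efficacy or safety, and that its design limits generalisation. The stated aim is to evaluate safety, and AE frequencies will be shown, with severity, duration and causality recorded. This stands, and it limits the point to a mismatch between claim and analysis.

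A second reply is that section 2.9 does not define its groups as individual medicines, so the splits and rates above are constructed. That also stands. A reader might infer that a doubled AE rate would usually be missed. The table does not support that: with 100 v 900 a doubling from 10% to 20% is found in 78% of cases, and with 200 v 800 in 95%.

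A third reply is that intervals may appear in the full protocol or analysis plan, which are not shown. Their absence from an article would indeed be no finding. What remains is in the text itself: section 2.9 commits all analyses to two-tailed tests, and the Discussion commits the results to verification.

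**Conclusion.** The point holds as an inconsistency between two statements in the article. The Discussion claims that hypotheses on the safety of herbal medicines will be verified and passed to a guideline, while the only inference stated in section 2.9 cannot establish safety. The verification wording also goes beyond the aim in the Introduction and sits poorly with the Discussion's own caveat.

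Its practical size depends on assumptions that the article does not supply, namely the AE rates and the users per formula. Within the range examined, it is serious for uncommon events at any split and for events of 5% to 10% in a group of about 100. It is small for common events in larger groups, and low power is not the issue for whole-cohort laboratory changes. The change is worth making because the results are meant for a guideline and the remedy uses data already planned.

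**What to change.** In section 2.9, base the safety evaluation on estimation:

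- Report the incidence of each template AE, any AE, and each liver or kidney test abnormality with an exact 95% confidence interval, overall and for each commonly used herbal medicine.
- Report any contrast between medicines as a risk difference or ratio with its 95% confidence interval.
- State that a non-significant test is not evidence of safety, or of equal safety between medicines.

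In the Discussion, replace the two verification phrases with a statement that the registry will estimate AE incidence with its confidence limits. That agrees with the aim in the Introduction and with the Discussion's caveat.

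The cost is a few sentences and standard output from the software already named, with no further patients or data. The downside is that safety statements about less-used formulas become visibly weaker, which reflects what the data can support.

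### The generic methods in section 2.9 are weak for the safety aim: averages can miss rare large laboratory rises, and crude AE percentages mix treatment length with risk

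*Protocol article*

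**What the plan says.** The Introduction lists two aims, and the second is to "evaluate the safety of various HMs for weight loss, based on nationwide registry outcome collecting process".

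Section 2.9 (Statistical analysis) gives one paragraph of methods for every variable. "Categorical variables will be presented as n (%) whereas continuous variables will be expressed as mean ± standard deviation". Groups are compared by chi-square or Fisher tests for categorical variables, and by t test, analysis of variance or rank tests for continuous ones. Pre-post change is tested by paired t or Wilcoxon signed rank test. Analysis of covariance is available where adjustment is needed, with demographic variables as the example. Missing values are filled by last observation carried forward. The tests are two-sided at 5%. Safety is not treated separately.

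Section 2.6 (Outcomes measures) lists AST, ALT, BUN and creatinine as the liver and kidney tests, and Table 1 schedules them at baseline and end of treatment. On exposure it says that "there will be no restriction on the type or frequency of HM treatment". AEs are asked about at each treatment visit and recorded with name, severity, duration and a causality assessment. The prescribed medicine, its composition and the treatment duration are also recorded.

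**The concern.** Drug-induced organ injury usually appears as a large rise in a few patients, not as a small shift in everyone. ALT and creatinine are continuous, so section 2.9 assigns them a mean, an SD and a test of average change. A handful of marked rises can disappear in that average, particularly if enzymes drift down in the other patients as they lose weight. Little else in the article would catch liver injury: the six AE types named in the Discussion are symptoms, none of them hepatic, although the AE template itself (Table 2) is not visible here.

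For AEs the difficulty is exposure. A patient treated for three months has more time, and probably more visits, in which an AE can arise and be recorded than a patient treated for one. A crude percentage of patients with an AE therefore reflects both the medicine and the length of the course.

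The Discussion says the safety results are to inform practice guidelines. A hidden signal, or a ranking of medicines driven by course length, could carry through to them.

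**Working it through.** **The plan's own figure.** "We plan to recruit at least 1000 patients during this study period", based on "approximately 1000 participants will be enrolled (65 patients or more per year per clinic) for a year" at 15 clinics. 15 × 65 = 975, which is 2.5% below 1000; 15 × 67 = 1005. The figure holds as an enrolment estimate, and N = 1000 is used below. The article gives no laboratory SD, drift, injury rate, AE hazard or course length, so all of these are assumptions shown over a range.

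**Laboratory tests.** Assume 1000 patients with both tests. In 990 the ALT change has mean δ and SD 15 U/L; in 10 (1%) it averages +200 U/L.

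- Mean change = 0.99δ + 0.01 × 200.
- SD of change = √(15² + 0.01 × 0.99 × (200 − δ)²).
- SE = SD/√1000, and the expected t is mean/SE.

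| Background drift δ | Mean change | SD | Expected t | Paired t shows a significant rise | Wilcoxon shows a significant rise |
|---|---|---|---|---|---|
| 0 | +2.00 | 24.9 | 2.54 | about 80% (83% to 84% in simulation) | 7% to 9% |
| −1 | +1.01 | 25.0 | 1.28 | about 13% (11% to 13%) | 0% |
| −3 | −0.97 | 25.2 | −1.22 | about 0% | 0% (significant fall in every run) |

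The percentages come from repeated simulations: 2000 runs for the t test and 200 to 500 for Wilcoxon.

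A second set of assumptions (change SD 12 U/L, each injured patient rising by 150 U/L) gives the same pattern. With 10 injured and no drift, the t test shows a rise in 79% of runs and Wilcoxon in 6%. With 5 injured and no drift the figures are 27% and 3%. With a 2 U/L background fall, neither test showed a rise at 5 or at 10 injured.

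Counting patients does not depend on the drift: 10 of 1000 is reported as 1.0%, exact 95% CI 0.48% to 1.83%.

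Section 2.9 adds one more weakness. With laboratory tests scheduled only at baseline and end of treatment, carrying the last value forward for a missing final test enters the baseline value, that is, a change of zero.

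**Adverse events.** With a constant hazard λ per month over t months, the expected proportion with at least one AE is 1 − exp(−λt). Give two medicines the same λ:

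| λ per month | 1 month | 3 months | Ratio | Significant at 100 per group | Significant at 500 per group |
|---|---|---|---|---|---|
| 0.05 | 4.9% | 13.9% | 2.86 | 59% | >99% |
| 0.10 | 9.5% | 25.9% | 2.72 | 87% | >99% |

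The gap shrinks when courses are closer in length. At λ = 0.10, 1 against 1.5 months gives 9.5% against 13.9%, significant in about 16% of cases at 100 per group and 58% at 500.

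The order can also reverse. A medicine with half the hazard (0.05 against 0.10) taken for 3 months instead of 1 shows 13.9% against 9.5%, and so looks worse.

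**The case against.** The strongest reply is that this is a condensed article, and that threshold counts, shift tables and person-time rates normally belong in an analysis plan that is not shown. Their absence alone would indeed be no finding. The point rests instead on the methods that are written down, which cover all analyses and make no exception for safety.

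A reader might infer that safety will be judged solely by mean laboratory change. The article does not say so. The sentence on n (%) and mean ± SD is a general presentation rule, and no safety criterion or decision rule is set. Nor does n (%) exclude a count of patients above a limit, since such a count is itself categorical.

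A reader might also infer that the second aim is to compare HMs. Its wording is to "evaluate the safety of various HMs for weight loss", and the groups to be compared in section 2.9 are not named. The exposure problem therefore applies to comparisons only if they are made.

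The magnitudes are assumed, and the laboratory result is sensitive to them: with no opposing drift, the t test usually does detect the 1% scenario. Groups of 500 on one medicine are also unlikely when treatment is individualised.

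Analysis of covariance could adjust continuous outcomes for treatment duration, but it does not suit a yes/no AE outcome. Finally, time-to-first-AE analysis needs onset dates, which the article does not list, and the study is already running. That limits one optional part of the remedy, not the rest.

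**Conclusion.** The point holds as a weakness in the stated methods for the safety aim. It is neither a contradiction in the article nor evidence that harm will be concealed.

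For laboratory safety, detection of a 1% rate of large ALT rises by the paired t test runs from about 80% to about 0% as the assumed background fall goes from 0 to 3 U/L. Wilcoxon detects it in under 10% of runs throughout. The opposing drift is an assumption, and the t test result depends on it.

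For AEs, equal hazards of 0.05 to 0.10 per month give nearly threefold differences in crude percentages between 1-month and 3-month courses. This matters where medicines are compared and their course lengths differ; the article leaves course length open and does not specify such a comparison.

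The change is worth making because the data it needs are, for the most part, already collected.

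**What to change.** Add the following to section 2.9, or confirm that the full analysis plan contains it.

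1. **Laboratory safety.** Among patients with both tests, report the number and percentage crossing prespecified multiples of the upper limit of normal for ALT/AST and creatinine, with exact 95% CIs and baseline-to-end shift tables. Use observed values, not carried-forward ones, and state how many patients lack a final test. Means and paired tests can stay as supporting description.
2. **Adverse events.** Report rates per person-month of recorded HM treatment with 95% CIs. Make any comparison between HMs with a Poisson or negative binomial model with log exposure as offset. Keep n (%) as description.
3. **Time to first AE.** Add cumulative incidence only if AE onset dates are available.

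Cost: a few extra tables, and dependence on the accuracy of recorded treatment duration. Items 1 and 2 use variables that section 2.6 already collects, together with each laboratory's reference limits. Item 3 could need a change to the case report form during recruitment, which is why it is conditional.
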